**Evaluating Stage**
Objective: Community-led co-creation of the intervention through community feedback and consensus on the agreed components of the intervention.Participants: Members of the initially engaged communities and technical group of CHMT members at the district level.Methods: After the initial data collected, they will be analysed using NVivo version 12 software for coding and for exploring outcome patterns and configurations of factors associated with the study outcomes. Once specific themes are obtained, the study team will present the findings back to communities to support the actual development of the intervention package. Conducting of the co-creation process through community feedback and nominal group techniques (NGTs) to manifest ownership and defining the intervention for implementation. It will be a free flow of ideas from the community member’s feedback and applicability of the co-created intervention will be put in the Rifkin’s CHOICE framework by the study team, along with appointed members of the community who will form a steering committee for the intervention. Iteration and refining of the intervention will be done through discussion, troubleshooting and feedback in the piloted wards before the scaling up to all the intervention wards. The NGT will be done through recording on a flipchart of main barriers and solutions from the conducting stage then discuss through them with the community members for priority setting.
**Scaling Stage**
The agreed local intervention will be scaled up in the rest of the intervention wards through the study component II. There are various models of scaling up but in our study we will use generalizable model in which the sampled local stakeholders will be representing the wider wards in which the intervention will be utilized. Once the planning committees of the selected communities have designed and established the details of their local interventions, a comparison across them to identify common elements will be done. The creation of a unified ‘intervention package’ to be used for all remaining intervention communities will follow.

**Figure 1. bpae016-F1:**
[figure not shown]
Community engagement and intervention co-creation flow diagram.*^a^TAMISEMI—regional and local authorities, ^b^MoH—Ministry of Health, Tanzania*

### Study component II: Effectiveness of the intervention implementation

#### Study design and target population

The second study component will be a two-armed, pragmatic, cRCT to estimate the effectiveness of the community-developed intervention implementation. The clusters in this case are administrative rural wards of Dodoma region. The study will be pragmatic in the sense participants and data collectors will not be masked to the allocation status of the ward, and no attempts will be made to prevent ‘contamination’ of control wards by research activities conducted in intervention wards, thereby allowing estimation of a more ‘real-world’ effectiveness of the intervention [33].

The primary focus of this portion of the study is the effectiveness of the community-led interventions in increasing uptake of eye health screening services and cataract surgery. Figure 2 explains the study flow for schedule of enrolment, interventions, and assessment.

**Figure 2 bpae016-F2:**
[figure not shown]
Study flow for schedule of enrolment, interventions, and assessment

### Study population and follow-up

Using data from the 2022 Tanzanian national census (accounting for predicted annual population growth of 2.7% up to the year 2023 for Dodoma region), we expect an average of 1420 adults aged 50 years and above in each study arm (coefficient of variation = 0.4).

Two years of follow-up will yield a mean of 2840 person-years of observation per intervention arm. Based on unpublished findings from a pilot study involving four wards conducted in 2020 by our research team we anticipate a screening rate (i.e. rate of presentation to screening camps among population >50 years of age) of 0.198 per person-year in control villages with an inter-village coefficient of variation (k) of 0.4. For cataract surgery, we anticipate a rate of 0.045 per person-year in control villages based on an estimated prevalence of visually significant cataract of 17.7%, and cataract surgical coverage of 25%. We conservatively assumed we would observe a level of inter-ward variation in surgery acceptance rates like that for screening rates (k = 0.4).

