## Methods and analysis

### Study area

The study will be conducted in Dodoma region of Tanzania. Dodoma is administratively divided into eight district councils. Currently, there are a total of 3.08 million people, 209 wards and people aged 50 years and above account for approximately 10% of the population [27]. Dodoma is one of the regions with the highest prevalence of cataract blindness at 17.7%, which is above the national average of 15% [28]. To address eye health care needs, the regional eye care team has established a regular eye outreach programme since 2017. This justify and favours the settings of this trial to be done in Dodoma region, as there is ongoing community eye outreach programmes (CEOP) aiming at screening patients at their communities. These were initiated by the regional health committee and they have not shown to be very promising in increasing cataract services uptake and henceforth this community-led trial is designed. The current CEOP is done twice each month by a team of assistant ophthalmic medical officers, optometrist, ophthalmic nursing officer, and a Programme coordinator. The main activities entail screening for refractive errors and simple eye diseases by use of a pen torch. Those needing further management and/or surgery are listed down and referred to a base hospital.

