### Sample size, randomization, and allocation concealment

Using the sample size calculation method for unmatched cRCTs described by Hayes and Bennett [34], it is calculated that 40 wards will need to be enrolled in each study arm to achieve 80% power to detect a minimum 30% increase in screening examination and cataract surgery acceptance rates associated with the intervention at the 95% confidence level.

Population data from the 2022 Tanzanian national census (accounting for predicted population growth up to 2023) will be used, we expect an average of 1420 adults aged over 50 years in each study ward (coefficient of variation = 0.43).

The sample size calculation method for unmatched cluster-randomized trials with rate outcomes described by Hayes and Bennett was used:
c=1+Zα/2+Zβ2λ0+λ1y+k2λ02+λ12/λ0-λ12where c is the number of clusters, $Z_{\alpha /2}$ is the standard normal distribution based on level of significance (1.96), $Z_{\beta }$ is the standard normal distribution value based on the power of $100\left(1-\beta \right)\%$ (using 80% power $Z_{\beta }=0.84)$, $\lambda_{0\;}$ and $\lambda_{1}$ rates of the outcome in absence and presence of intervention, respectively, y is the person-years of follow-up in each group ward, and k = 0.4 is the coefficient of variation of the population rates between wards within each group. To detect a minimum 30% difference in outcome rates comparing intervention to control wards, we calculate that we will need to enrol 39 wards in each study arm for the presentation at screening camps outcome (outcome 1), and 42 wards in each arm for the cataract surgery outcome (outcome 2). To sufficiently power the study for both outcomes, we will sample a total of 40 wards in each study arm taking into account the design effect as well.

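### The control surgery rate of 0.045 per person-year is prevalence times coverage, not an annual rate, so surgery power should be restated over a range of true annual rates

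*Protocol article*

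**What the plan says.** The Protocol article sets two control rates under Study population and follow-up. For screening, "we anticipate a screening rate (i.e. rate of presentation to screening camps among population >50 years of age) of 0.198 per person-year", taken from an unpublished four-ward pilot in 2020. For surgery, "we anticipate a rate of 0.045 per person-year in control villages based on an estimated prevalence of visually significant cataract of 17.7" per cent, and on a surgical coverage of 25%. The between-ward coefficient of variation k is 0.4 for screening, and the same value is assumed for surgery.

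Under Sample size, randomization, and allocation concealment, these rates enter the Hayes and Bennett formula for unmatched clusters with rate outcomes, where y is person-years per ward. "To detect a minimum 30% difference in outcome rates comparing intervention to control wards", the plan obtains 39 wards per arm for screening and 42 for surgery, and adopts 40.

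Two other places bear on the surgery rate. Data collection procedure describes surgery as following from camps: attenders found to have operable cataract are counselled and referred to the base hospital. Study area gives the 17.7% another label: "Dodoma is one of the regions with the highest prevalence of cataract blindness at 17.7" per cent.

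**The concern.** Prevalence is a proportion at a point in time. Coverage, multiplied directly by prevalence as it is here, acts as the share of that stock which has been treated. Neither factor is per year, so their product is a share of residents and not an incidence. The formula needs events per person-year, and the article gives no step that turns one into the other.

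The result also fits poorly with the plan's own screening rate. The term in the formula for chance variation in event counts grows as the rate falls, so if the true control rate is below 0.045, the wards needed for surgery are understated and the power overstated. Surgery is the outcome named under Primary outcome, although the abstract lists screening as a second primary.

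**Working it through.** **1. Inputs.** Control surgery rate λ0 = 0.045, prevalence 17.7%, coverage 25%, control screening rate 0.198, k = 0.4 and two years of follow-up (Study population and follow-up). Rate ratio 1.3, z-values 1.96 and 0.84, 1420 adults per ward, 40 wards per arm (Sample size section). Two years of 1420 adults is 2840 person-years. The article attaches 2840 to an arm, but the formula needs it per ward, so both y = 2840 and y = 1420 are shown.

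**2. Origin of 0.045.** 0.177 × 0.25 = 0.04425, close to 0.045. No time period enters.

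**3. The plan's own ward numbers.** The formula is

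c = 1 + (1.96 + 0.84)² × [(λ0 + λ1)/y + k²(λ0² + λ1²)] / (λ0 − λ1)².

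With λ1 = 1.3 λ0 it reduces to

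c = 1 + 7.84 × [2.3/(λ0·y) + 0.16 × 2.69] / 0.09 = 38.5 + 200.4/(λ0·y).

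- Screening, 0.198: 39.2 wards at y = 1420; 38.8 at y = 2840.
- Surgery, 0.045: 41.6 wards at y = 1420; 40.1 at y = 2840.

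Only y = 1420 gives both stated figures, 39 and 42, to the nearest ward. The 38.5 comes from k alone, whatever the rate.

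**4. Against the screening rate.** If attenders have the population prevalence, camps find 0.198 × 0.177 = 0.0350 cases per person-year. Reaching 0.045 would then take 0.045/0.0350 = 128% acceptance. Put the other way, 0.045/0.198 = 22.7% of attenders must have surgery. That means at least 22.7% with operable cataract at full acceptance, or 45% at half acceptance.

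**5. Against the stated coverage.** Over two years 0.045 gives 0.09 operations per adult, and 0.09/0.177 = 51% of the prevalent pool under control conditions. The stated coverage is 25%.

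**6. Power with 40 wards per arm.** Inverting the formula, power = Φ(√{39 × 0.09 / [2.3/(λ0·y) + 0.4304]} − 1.96).

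| Control rate | Basis | Wards needed, y = 2840 / 1420 | Power at 40 wards, y = 2840 / 1420 |
|---|---|---|---|
| 0.045 | as stated | 40.1 / 41.6 | 79.9% / 78.3% |
| 0.035 | population prevalence among attenders, all accept | 40.5 / 42.5 | 79.4% / 77.4% |
| 0.022 | 0.04425 spread over two years | 41.7 / 44.9 | 78.3% / 75.2% |
| 0.0175 | 0.035 with 50% acceptance (assumed) | 42.5 / 46.5 | 77.4% / 73.6% |
| 0.0088 | 0.035 with 25% acceptance (assumed, illustrative) | 46.5 / 54.6 | 73.6% / 66.6% |

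**The case against.** **The rate is possible.** A reader might infer that 0.045 cannot arise from a screening rate of 0.198. The documents do not support that. Only 22.7% of attenders need have surgery. People with poor sight may be likelier to attend an eye camp, and the article does not say that camp referral is the only route to surgery that is counted. This stands: the rate is unsupported, not impossible.

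**The stated 42 wards may survive.** For a fixed rate ratio and k, the formula depends on the rate only through λ0·y. The plan's apparent inputs give 0.045 × 1420 = 63.9 events per ward, the same as 0.0225 × 2840. If 0.045 is a two-year proportion and y should be 2840, the answer is still 42. This stands for that one reading, but the article labels the figure per person-year and nowhere says that the 25% coverage builds up over two years.

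**There is no acceptance figure.** The lowest rates in the table need acceptance among attenders with cataract, which the article does not give. Using the 25% coverage for it may discount non-attendance twice, since a population share already reflects people who never attend. This stands, so the 0.0088 row is an illustration, not an estimate.

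**The 51% comparison is rough.** It ignores cataract that develops during the two years. It signals inconsistency and does not prove error.

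None of this supplies the missing time unit.

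**Conclusion.** The point holds as an error in a stated input. The 0.045 is a cumulative proportion entered as an annual rate, and the plan's other figures support it only with enriched attendance or surgery outside the camps, neither of which is stated.

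The size is modest. A reader might infer that the trial is seriously underpowered for surgery; the documents do not show that. Any lower rate reduces power, but k = 0.4 alone accounts for 38.5 wards. Relative to the stated rate, the loss is 0.5 to 0.9 percentage points at 0.035 and 1.6 to 3.1 points at 0.022. It reaches 6.3 to 11.7 points only at the illustrative 25% acceptance. These figures rest on k = 0.4 and a 30% increase; the 0.035 and acceptance-based rows also assume population prevalence among attenders.

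Part of the shortfall from 80% has a separate cause: 40 wards is below the plan's own 42, so with y = 1420 power is 78.3% even at 0.045. The two labels for the 17.7% have no numerical effect that can be shown from the document, but they leave unclear which condition the rate is built on.

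**What to change.** - Replace 0.045 with a true annual rate of surgery per person-year in adults aged 50 and over. Use surgery counts from the 2020 pilot if they exist; the article credits only the screening rate to it. Otherwise use screening rate × operable fraction among attenders × acceptance, with each factor and its source stated.
- State which y is used, per ward.
- Restate surgery power at 40 wards per arm over a range of rates, including the 0.045 baseline and the 0.035 case as well as the lower ones.
- Use one definition for the 17.7%, and say how it relates to operable cataract as defined under Data collection procedure.

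The cost is a recalculation and a slightly less favourable stated power. No extra wards are required.

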### Sample size, randomization, and allocation concealment

Using the sample size calculation method for unmatched cRCTs described by Hayes and Bennett [34], it is calculated that 40 wards will need to be enrolled in each study arm to achieve 80% power to detect a minimum 30% increase in screening examination and cataract surgery acceptance rates associated with the intervention at the 95% confidence level.

Population data from the 2022 Tanzanian national census (accounting for predicted population growth up to 2023) will be used, we expect an average of 1420 adults aged over 50 years in each study ward (coefficient of variation = 0.43).

The sample size calculation method for unmatched cluster-randomized trials with rate outcomes described by Hayes and Bennett was used:
c=1+Zα/2+Zβ2λ0+λ1y+k2λ02+λ12/λ0-λ12where c is the number of clusters, $Z_{\alpha /2}$ is the standard normal distribution based on level of significance (1.96), $Z_{\beta }$ is the standard normal distribution value based on the power of $100\left(1-\beta \right)\%$ (using 80% power $Z_{\beta }=0.84)$, $\lambda_{0\;}$ and $\lambda_{1}$ rates of the outcome in absence and presence of intervention, respectively, y is the person-years of follow-up in each group ward, and k = 0.4 is the coefficient of variation of the population rates between wards within each group. To detect a minimum 30% difference in outcome rates comparing intervention to control wards, we calculate that we will need to enrol 39 wards in each study arm for the presentation at screening camps outcome (outcome 1), and 42 wards in each arm for the cataract surgery outcome (outcome 2). To sufficiently power the study for both outcomes, we will sample a total of 40 wards in each study arm taking into account the design effect as well.

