### Overall study design

This protocol paper is structured conforming to the Standard Protocol Items: Recommendations for Intervention Trials (SPIRIT) 2013 Checklist [29]. The project will be having two components as (i) Intervention co-creation component using participatory action research approaches [i.e. Focus Group Discussions (FGDs), and Key Informant Interviews (KIIs)] (ii) Assessment of effectiveness and scaling of the intervention through a cRCT. A community-led participatory action research design was chosen because the intervention development and implementation will largely be locally designed and adapted by communities. A community-led participatory action research study design offers an ideal opportunity to engage the community at every stage to develop their own intervention package and implemented for assessment of effectiveness of the interventions, the role of implementation factors, and strategies facilitating the sustainability and scaling up of the intervention package. The cRCT was chosen because it avoids the selection biases and provides a robust way of getting strong correlation of study variables. In this setting, a cluster is defined as an administrative ward which usually has a typical population ranging from 8000 to 12,000.

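### The sample-size section calculates 42 wards per arm for surgery, enrols 40, and still claims 80% power for both outcomes; the shortfall is small and the text needs correcting

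*Protocol article*

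**What the plan says.** The section on sample size, randomization, and allocation concealment makes three statements about the number of wards.

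- It opens with the result: "40 wards will need to be enrolled in each study arm to achieve 80% power", for a 30% increase in both the screening and the surgery rates.
- After the formula it gives separate results: 39 wards per arm for attendance at screening camps, and "42 wards in each arm for the cataract surgery outcome (outcome 2".
- It concludes: "To sufficiently power the study for both outcomes, we will sample a total of 40 wards in each study arm". The same sentence adds that the design effect has been taken into account.

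The abstract and the eligibility section confirm 80 wards in total, randomized 1:1.

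The size of the population is described in two ways. Under Study population and follow-up: "we expect an average of 1420 adults aged 50 years and above in each study arm (coefficient of variation = 0.4", with two years of follow-up giving 2840 person-years, again per arm. The sample-size section gives the same 1420 adults per ward, and its formula defines person-years per ward.

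Surgery acceptance is one of two primary outcomes in the abstract and the only one under Primary outcome in the Methods.

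**The concern.** A requirement of 42 and an enrolment of 40 cannot both go with 80% power for surgery. The outcome left short is a primary one on either listing of the outcomes.

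The design-effect remark reads as if an extra allowance had been made. None can have been, because the final number lies below the larger of the two calculated ones. Between-ward variation is already in the formula through k, so a further design effect would count it twice, and in any case it could only raise the ward count.

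A reader who tries to settle the matter by repeating the calculation is hindered by the per-arm wording for the 1420 adults and 2840 person-years. The section also does not say which person-years figure was used. At stake is whether the stated power for the main outcome can be relied on and checked.

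**Working it through.** **Inputs**

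- Two-sided 5% level: y-independent term z = 1.96 ("is the standard normal distribution based on level of significance (1.96"). Power 80%: z = 0.84. So (1.96 + 0.84)² = 7.84.
- Effect: "to achieve 80% power to detect a minimum 30% increase in screening examination and cataract surgery acceptance rates", so λ1 = 1.3 λ0.
- Surgery: "For cataract surgery, we anticipate a rate of 0.045 per person-year in control villages", so λ0 = 0.045 and λ1 = 0.0585.
- Screening: λ0 = 0.198 (Study population and follow-up), so λ1 = 0.2574.
- k = 0.4 for both outcomes, so k² = 0.16.
- y, person-years per ward: 1420 adults × 2 years = 2840, or 1420 for one year.

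**Formula** (the one the section cites for unmatched clusters with rate outcomes)

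c = 1 + 7.84 × [(λ0 + λ1)/y + k²(λ0² + λ1²)] / (λ0 − λ1)²

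**Screening, y = 2840**

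- (λ0 + λ1)/y = 0.4554/2840 = 0.0001604
- k²(λ0² + λ1²) = 0.16 × 0.1054588 = 0.0168734
- (λ0 − λ1)² = 0.0594² = 0.0035284
- c = 1 + 7.84 × 0.0170338/0.0035284 = 38.85, rounded up to 39. This is the printed figure.

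**Surgery, y = 2840**

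- (λ0 + λ1)/y = 0.1035/2840 = 0.00003644
- k²(λ0² + λ1²) = 0.16 × 0.00544725 = 0.00087156
- (λ0 − λ1)² = 0.0135² = 0.00018225
- c = 1 + 7.84 × 0.00090800/0.00018225 = 40.06, rounded up to 41. This is one ward below the printed 42.

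**Surgery, y = 1420**

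- The first term doubles to 0.00007289.
- c = 1 + 7.84 × 0.00094445/0.00018225 = 41.63, which gives the printed 42.

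**Screening, y = 1420**

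- The first term becomes 0.0003207, and c = 39.21: 40 if rounded up, 39 if rounded to the nearest ward.

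**Power with 40 wards per arm**

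Inverting the formula, power = Φ(2.8 × √[39/(c − 1)] − 1.96), with c unrounded.

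| Outcome | y per ward | c | Power at 40 |
|---|---|---|---|
| Screening | 2840 | 38.85 | Φ(0.882) = 81.1% |
| Screening | 1420 | 39.21 | Φ(0.869) = 80.8% |
| Surgery | 2840 | 40.06 | Φ(0.838) = 79.9% |
| Surgery | 1420 | 41.63 | Φ(0.783) = 78.3% |

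A noncentral t calculation with 78 degrees of freedom gives the same 81.1% for screening (y = 2840), and 79.9% and 78.3% for surgery.

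**The case against.** The strongest reply is that the printed 42 is the slip and that the enrolment and the power claim are sound. On two years of follow-up, 40 wards give 79.9% power for surgery, which is 80% to the nearest percent. That stands as to size: nothing here calls for a different design. It does not remove the contradiction, because the section prints 42 as its own requirement and offers a reason for 40 that cannot be right.

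A reader might go further in four ways that the documents do not support.

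- *That 42 cannot be reproduced.* It can, from one year of person-time with 1420 adults per ward, and it is only one ward above the two-year result.
- *That the two counts must rest on different person-years.* This follows only if both were rounded up. Rounded to the nearest ward, y = 1420 gives both 39 and 42, and the article states no rounding rule.
- *That 1420 older adults per ward is wrong.* The Overall study design section describes a ward as one "which usually has a typical population ranging from 8000 to 12,000"; with about 10% aged 50 or over, that gives 800 to 1200. But the Study area section gives 3.08 million people in 209 wards, so 3,080,000/209 ≈ 14,737 people and about 1474 older adults per ward, close to 1420. The loose range is not an input to the calculation.
- *That the trial is far too small because 1420 is the number per arm.* The sample-size section gives the same figure per ward and defines y per ward, which rules that reading out. The per-arm wording is a slip.

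**Conclusion.** The point holds as an internal contradiction: 42 wards calculated for surgery, 40 enrolled, and 80% power claimed for both outcomes, with a design-effect remark that does not explain the difference.

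The shortfall for surgery is about 0.1 percentage points if y is 2840 per ward and about 1.7 if it is 1420. Screening reaches about 81% on either figure. These results take the stated rates, k = 0.4 and the 30% increase as given, and read 1420 adults as per ward. Which person-years figure the authors used for surgery cannot be established from the article.

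This is a minor correction to a stated figure. It does not show that the trial is underpowered in any important way.

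**What to change.** Keep 40 wards per arm and correct the text:

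- State one y per ward and use it for both outcomes.
- Make the ward counts agree with it. Rounded up, y = 2840 gives 39 for screening and 41 for surgery; y = 1420 gives 40 and 42.
- Replace the claim of 80% power for both outcomes, in the opening and in the closing sentence, with the power achieved: about 81% for screening, and for surgery 79.9% (y = 2840) or 78.3% (y = 1420).
- Delete the design-effect remark.
- Under Study population and follow-up, change per arm to per ward for the 1420 adults and the 2840 person-years.

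The cost is wording only, with a slightly less favourable stated power for surgery. Enrolling 42 wards per arm (84 in total) would also remove the contradiction, with about 82% power for surgery at y = 2840 and 80% at y = 1420, but a gap this small does not require it.
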